### Sample size

2.4

The frequency of acute exacerbations is the primary outcome. According to the data in previous studies, the annual frequency of acute exacerbations in the control group was 1.08 episodes (27), and the experimental group is expected to have a 40% reduction (28), i.e., 0.648 episodes. The test level (*α*) and power (1 − *β*) of the hypothesis test were set at 0.05 and 0.9, and the sample size ratio of the experimental group and control group was 1:1. The estimated sample size for each group was 359 participants using PASS software. After accounting for a 15% dropout rate, the required sample size per group was adjusted to 423 participants. Due to the centralized blocked randomization with block sizes of 4, the sample size per group was adjusted to 424 participants. A total of 848 subjects will be enrolled in this trial.

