#### Secondary outcomes

2.7.2

Secondary outcomes include the following indicators:

(1) Number of AECOPD episodes leading to hospitalization: Hospitalizations due to AECOPD should be promptly recorded in the study diary. The frequency should be recorded every 13 weeks during the study period.(2) Mortality: At the end of the study, the mortality of the two groups will be measured, including the AECOPD-related mortality and all-cause mortality.(3) Lung function: Tests will include forced vital capacity (FVC), forced expiratory volume in 1 second (FEV1), FEV1% predicted, and FEV1/FVC. Measurements will be conducted at baseline and every 13 weeks during the study period.(4) Clinical symptoms and signs scores: Assessments will cover cough, expectoration, wheezing, chest tightness, fatigue, cyanosis, etc. Each item will be scored on a 0–3 scale. Higher scores indicate worse disease status. Evaluations will be performed at baseline and every 13 weeks after the start of the trial.(5) Six-minute walking distance (6MWD): The total distance walked by patients on a flat surface within 6 min reflects exercise capacity. A greater distance indicates better exercise capacity (29). 6MWD will be measured at baseline and every 13 weeks during the study period.(6) Quality of life: The COPD assessment test (CAT) and 36-item short-form health survey (SF-36) are used to assess the quality of life of patients. A higher SF-36 score indicates better quality of life, while a higher CAT score indicates worse quality of life (30, 31). These questionnaires will be administered at baseline and every 13 weeks after trial initiation.

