#### Quality control

2.8.2

In order to ensure the quality of this trial, we will establish a quality control committee and a data monitoring committee (DMC). DMC comprises 3 independent experts (1 statistician, 1 pulmonologist, and 1 TCM specialist) with no affiliations to the sponsors or research centers. The committee conducts monthly evaluations on the following aspects: protocol adherence (consistency of interventions, compliance with inclusion and exclusion criteria), data accuracy (verification of 10% of CRFs against original documents), and safety profile (analysis of adverse events). Researchers will comply with the guidelines of good clinical practice (GCP). Quality control experts will conduct monthly quality control assessments to ensure the quality of the study. Additionally, all researchers will receive standardized training on the study protocol. Last but not least, enhancing participants’ compliance is another important measure for quality control. Strategies to improve compliance include monthly telephone follow-ups with participants, quarterly home visits for participants, provision of health education materials, and offering appropriate subsidies, etc.

Additionally, an interim analysis will be conducted by the DMC when 50% of follow-up data are accumulated, assessing efficacy, safety, and futility using the O’Brien-Fleming alpha spending function to control type I error. The DMC will recommend continuation, early termination, or modification based on results. Blinding effectiveness will be evaluated post-trial via questionnaires for investigators and participants to guess group allocation. Correct guess proportions will be compared with 50% (random chance) using the chi-square test; non-significant deviation indicates successful blinding.

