### Statistical analysis

2.9

SPSS software (Version 25.0) will be used for statistical analysis in this study. The study data will be analyzed according to the ITT principle, where all randomized participants will be included in the analysis according to their original group assignment, regardless of protocol deviations or different follow-up durations. For participants with varying follow-up durations, mixed-effects models for repeated measures will incorporate time as a covariate to utilize available data. Missing data will be handled using mixed-effects models for repeated measures as the primary method, with multiple imputation conducted as a sensitivity analysis. Continuous variables will be expressed as either mean ± standard deviation (assuming normal distribution) or median (interquartile range) (non-normal distribution). For the primary outcome, Poisson regression or negative binomial regression will be used based on overdispersion tests (assuming Poisson or negative binomial distribution). For secondary outcomes: count data will use the same methods as the primary outcome; binary data will use logistic regression (assuming binomial distribution); continuous data will use repeated-measures analysis of variance (for normal distribution) or Friedman test (for non-normal distribution). Mauchly’s test will first be applied to assess sphericity for repeated measures. If the assumption is violated (*p* < 0.05), the Greenhouse–Geisser correction will be implemented. Pairwise comparisons within groups will use the Bonferroni method, between groups the LSD-*t* test (equal variances) or Tamhane’s T2 method (unequal variances). Categorical variables will be presented as frequency (%) and compared using the chi-square test (large samples) or Fisher’s exact test (small samples with <5 expected counts). Outliers will be identified using box plots (values beyond 1.5 × interquartile range), verified for data accuracy, and retained in the primary analysis; sensitivity analyses excluding outliers will be conducted. For all statistical tests, both *p*-values and 95% confidence intervals will be reported. A hierarchical testing strategy will be used for multiple comparisons: the primary outcome will be tested first; if significant, secondary outcomes will be tested with Bonferroni correction to control type I error, aligning with the outcome hierarchy. A *p*-value <0.05 is considered statistically significant.

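### The count model for AECOPD and hospitalised AECOPD is picked by an overdispersion test on the trial's own data; fixing negative binomial regression at both looks is a cheap, minor improvement

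*Protocol article*

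**What the plan says.** For the primary outcome, section 2.9 (Statistical analysis) states that "Poisson regression or negative binomial regression will be used based on overdispersion tests". It then says of secondary outcomes that "count data will use the same methods as the primary outcome". Section 2.7.2 lists one such outcome, "Number of AECOPD episodes leading to hospitalization".

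Section 2.8.2 (Quality control) adds that "an interim analysis will be conducted by the DMC when 50% of follow-up data are accumulated", covering efficacy, safety and futility with O'Brien-Fleming alpha spending. It does not say whether the count model is settled once or chosen again at each look.

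Section 2.9 also limits when secondary outcomes are tested: only after a significant primary result, and then with Bonferroni correction.

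**The concern.** The choice between Poisson and negative binomial regression is made from the outcome data. If the test is not significant, Poisson is kept, although a non-significant result does not show that overdispersion is absent. If Poisson is kept for overdispersed counts, its standard errors are too small and a nominal 5% test rejects too often.

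Some overdispersion tests behave badly when the mean count is low, and hospitalised AECOPD is rarer than AECOPD overall. The interim look, with less exposure per patient, also lowers the mean. The primary test at the interim and at the final analysis could therefore come from different models, while alpha spending is normally thought of as following one statistic over time.

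**Working it through.** **The plan's own figures.** The protocol states no error rate for the selection rule, so there is none to reproduce. Section 2.4 is the only source for the size of the counts: "the annual frequency of acute exacerbations in the control group was 1.08 episodes", "the experimental group is expected to have a 40% reduction" (0.648), and alpha and power that "of the hypothesis test were set at 0.05 and 0.9". The null mean used here is (1.08 + 0.648)/2 = 0.864 per year.

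- Poisson, two-sided, n per group = 10.507 × (1/1.08 + 1/0.648)/(ln 0.6)² = 10.507 × 2.469/0.2609 = 99.4, not the stated 359.
- Adding a negative binomial dispersion k: 10.507 × (2.469 + 2k)/0.2609 = 359 gives k = 3.22. The plan does not state this value. It serves here only to show that dispersion up to about 3 is worth examining. Applying it to hospitalisations is an assumption.
- 359/0.85 = 422.4, so 423, then 424 for the blocks. This agrees with the plan.

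**Method.** Gamma-Poisson counts with no treatment effect were simulated, mainly at 359 per group. A 5% overdispersion test was followed by a two-sided 5% Wald test from the chosen model.

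**Primary count, final look.** With rates 0.648 to 1.08 and dispersion 0.1 to 2, type I error was 4.0 to 5.6% with every test tried (Monte Carlo standard error about 0.6 points). At dispersion 0.5 or more, Poisson was kept in at most 0.3% of runs. Using Poisson always would have given up to 28%, so the rule protects the primary test.

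**Hospitalised AECOPD, deviance test.** When Poisson is kept, the true level is about 2 × [1 − Φ(1.96/√(1 + kμ))]. For μ = 0.2 and k = 3, 1 + kμ = 1.6, 1.96/√1.6 = 1.55, and the level is about 12%. Simulation (20,000 runs per cell, with a Pearson-scaled standard error standing in for negative binomial after rejection) gave:

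| Rate per year | k = 1 | k = 2 | k = 3 | Poisson kept |
|---|---|---|---|---|
| 0.15 | 6.7% | 8.4% | 10.6% | 100% |
| 0.20 | 6.9% | 9.2% | 12.1% | about 100% |
| 0.25 | 7.5% | 10.9% | 13.5% | 97 to 100% |
| 0.30 | 8.5% | 11.0% | 10.7% | 55 to 100% |
| 0.35 | 8.6% | 7.7% | 6.2% | 9 to 92% |

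At 0.1 per year, a separate simulation (360 per group, dispersion 1 to 3.2) gave 5.9 to 8.9%. At 0.5 per year the level returned to about 4 to 6%, because the deviance test then rejects Poisson.

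**Hospitalised AECOPD, other tests.** With Pearson, score or likelihood-ratio tests, type I error was within 0.5 points of always using negative binomial in every setting.

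**At the Bonferroni level.** The number of secondary tests is not stated. Taking six for illustration, 0.05/6 = 0.83% corresponds to z = 2.638. With a variance/mean ratio of 1.6, 2.638/√1.6 = 2.086, which gives about 3.7%. The relative inflation persists, but the absolute rate is lower.

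**Interim against final, primary count.** If half the patients are complete at the interim, the Poisson/negative binomial decision differs between looks in 21 to 26% of runs at dispersion 0.1, in at most 12% at 0.3 and in almost none from 0.5 up. If instead every patient has half exposure, it differs more often, above all with a deviance test. The effect on error is small. At an interim mean of 0.432, Poisson understates the standard error by √(1 + 0.432k): 1.02 at k = 0.1, 1.06 at k = 0.3 and 1.10 at k = 0.5. Against an O'Brien-Fleming interim boundary of about z = 2.96 (nominal 0.3%), the interim error becomes about 0.4%, 0.5% and 0.7%.

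**The case against.** The strongest reply is that the rule works where it matters most. The primary test keeps its level, and the inflation for hospitalised AECOPD needs three inputs that the protocol does not supply: a deviance test, a low rate and substantial dispersion. A deviance check is poorly suited to sparse counts, and a competent analyst may well use another test. The test and its threshold can properly be left to an analysis plan that is not shown. The gatekeeping also counts: if the granules affect neither outcome, a false hospitalisation claim can follow only a false primary result.

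Most of this stands, and it is why the point is minor. Two parts do not. First, choosing the model from the outcome data is the stated rule, not an omitted detail; naming a test later would leave it in place. Second, gatekeeping does not correct the hospitalisation test once the primary result is truly positive.

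A reader might infer three stronger things that the document does not support:

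- That hospitalised AECOPD will be tested at 12% or some similar figure. Any single value rests on assumed inputs and ignores the Bonferroni level.
- That a change of model between looks damages the alpha spending. It arises mainly with mild overdispersion, where the two models nearly agree. Enrolment is staggered (Trial status: July 2024 to December 2025), so the every-patient-at-half-exposure case is also extreme.
- That the rule lets the more favourable result be picked. As written, it selects on dispersion, not on the treatment effect.

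**Conclusion.** The point holds in a limited form and is of minor severity. The model is data-driven for both counts, and nothing shown keeps it the same at both looks. The consequence for the primary type I error is negligible. For hospitalised AECOPD it ranges from none (Pearson, score or likelihood-ratio test, or a rate near 0.5 per year) to about 6 to 13% at a nominal 5% (deviance test, assumed rates 0.1 to 0.3 per year, assumed dispersion 1 to 3). That range applies only after a significant primary result and before Bonferroni correction. It is not a ceiling: at 0.2 per year and dispersion 4 the simulated level was about 14 to 16%. The case for change is that the validity of a secondary test should not turn on which overdispersion test is used, when avoiding this costs almost nothing.

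**What to change.** In section 2.9, replace the selection rule with wording such as: *The number of AECOPD and the number of AECOPD leading to hospitalisation will be analysed by negative binomial regression (log link, dispersion estimated from the data, not fixed) at both the interim and the final analysis. No overdispersion test will be used to choose the model. If the model does not converge, Poisson regression with robust variance will be used.* Report the estimated dispersion.

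The fallback still depends on the data, but only on a computing failure, and it is named in advance. Simulated type I error for negative binomial fixed in advance was about 4 to 6% for AECOPD and 4 to 7% for hospitalised AECOPD, consistent with 5% within Monte Carlo error.

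The cost is one sentence and some power if the counts are truly Poisson: 87.1% instead of 87.6% in the simulation. At the planned rates about 99 per group would already give 90% power under Poisson, so with 359 the loss there would be smaller still. Analysis is scheduled from March 2027 (Trial status), but the interim look comes earlier, so the change should be made before it.

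### Continuous secondary outcomes are assigned to repeated-measures ANOVA or to a Friedman test with no arm factor, against the plan's own all-randomised, mixed-model rule

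*Protocol article*

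**What the plan says.** Section 2.9 (Statistical analysis) makes three statements that bear on the continuous secondary outcomes.

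- **Population.** Under the ITT principle, "all randomized participants will be included in the analysis according to their original group assignment".
- **Missing data and unequal follow-up.** "Missing data will be handled using mixed-effects models for repeated measures as the primary method, with multiple imputation conducted as a sensitivity analysis". For unequal follow-up, "mixed-effects models for repeated measures will incorporate time as a covariate to utilize available data". Section 2.3.4 (Withdrawal/termination criteria) repeats the rule for patients lost to follow-up.
- **Test.** "continuous data will use repeated-measures analysis of variance (for normal distribution) or Friedman test (for non-normal distribution"). A sphericity check by Mauchly's method comes next, with the Greenhouse–Geisser adjustment if sphericity fails. On follow-up tests the section states: "Pairwise comparisons within groups will use the Bonferroni method, between groups the LSD". The LSD procedure is specified as a t-test, and Tamhane's T2 takes its place when variances are unequal.

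Section 2.7.2 and Table 2 schedule these outcomes at baseline and at weeks 13, 26, 39 and 52, so there are five occasions. Section 2.9 assigns the primary outcome and the other count outcomes to Poisson or negative binomial regression, and binary outcomes to logistic regression. No outcome is expressly assigned to the mixed model.

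**The concern.** Two different analyses are named for the same outcomes. A mixed model uses whatever visits a patient has. Classical repeated-measures ANOVA, which is where the Mauchly and Greenhouse–Geisser steps belong, needs a value at every visit. Two analysts following section 2.9 in good faith could report different sets of patients and different estimates. If missed visits are related to how patients are doing, the ANOVA result describes completers and may be biased.

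The non-normal branch has a further problem. The Friedman test asks whether values change across visits within patients. It does not ask whether the arms differ, which is the trial's question. Bounded or item-based scales such as the 0–3 symptom items, CAT and SF-36 are the likeliest to be sent down this branch.

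**Working it through.** **1. The plan's own figure.** Section 2.4 gives 359 per group and a 15% dropout rate. 359 / (1 − 0.15) = 422.4, rounded up to 423. The next multiple of the block size of 4 is 424, and 2 × 424 = 848. The plan's arithmetic is reproduced.

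**2. Patients lost under ANOVA.** Patients retained = 848 × (1 − d), where d is the proportion with at least one missing visit.

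| d | Retained | Left out |
|---|---|---|
| 5% (assumed) | 805.6, about 806 | about 42 |
| 10% (assumed) | 763.2, about 763 | about 85 |
| 15% (section 2.4 allowance) | 720.8, about 721 | about 127 |

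The 15% row assumes that the allowance is fully used and that each dropout lacks at least one visit. A mixed model with baseline as covariate keeps every patient who has a baseline value and at least one later value. Multiple imputation could fill the gaps for the ANOVA, but section 2.9 reserves it for sensitivity analysis.

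**3. What the Friedman test responds to.** The simulation used 360 patients per arm, five occasions, between-patient SD 1, within-patient error SD 1 and 2,000 replicates. All of these settings are assumptions. Shifts apply to the four post-baseline visits and are in units of the error SD.

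| Scenario | How run | Result at 0.05 |
|---|---|---|
| No change, no arm difference | pooled over arms | rejects in 4.6% |
| Both arms shift by 0.3, no arm difference | pooled over arms | rejects in 100% |
| Arms shift by +0.3 and −0.3, true difference 0.6 | pooled over arms | rejects in 4.6% |
| Both arms shift by 0.12, no arm difference | separately by arm | significant in exactly one arm in 38% |

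Pooled, the test fires on a change shared by both arms and does no better than chance on a real arm difference that cancels over the pooled sample. The third scenario is deliberately extreme, but it shows that no term in the test carries the treatment effect. Run arm by arm, the rejection rates in the last scenario were 0.2515 and 0.2525. Discordant results are then expected in 0.2515 × 0.7475 + 0.2525 × 0.7485 = 0.377 of trials, although the arms do not differ. Setting one arm's p-value beside the other's is therefore not a substitute for a comparison.

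**4. Is there another between-arm test for skewed data?** Section 2.9 names only LSD-t and Tamhane's T2 for between-group comparison of continuous outcomes. Both are parametric, and both are meant for three or more groups. With two arms, LSD is simply a t-test. No rank-based between-arm test is named.

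No power figure can be given, because the article states no SD or expected effect for any continuous secondary outcome.

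**The case against.** The strongest defence is that the mixed-model rule governs incomplete data, so the ANOVA label is loose wording for a mixed-model analysis. The article nowhere says complete-case. That is a possible reading, but the sphericity test and its correction belong to classical ANOVA and not to such a model, and the text does not join the two. The loss of 127 patients is therefore the consequence of one reading and not a stated intention. It is also an upper-end figure in one respect: 15% is a sample-size allowance, and section 2.3.4 keeps patients who stop treatment in follow-up.

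Three stronger inferences are tempting, and the article does not support them.

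- **That the plan gives no treatment comparison at all.** For normal data the ANOVA has group and group-by-time terms, and the LSD-t/Tamhane sentence supplies a parametric arm comparison that is not expressly limited to the normal branch. With about 360 per arm, a comparison of means usually tolerates moderate skew. What is missing is a valid rank-based arm comparison in the branch that calls for one.
- **That unadjusted visit-by-visit t-tests undo the type I error control.** Section 2.9 tests secondary outcomes only if the primary is significant, and then with Bonferroni correction. An error rate computed with every visit tested at 0.05 ignores that rule. The fair remark is that the rule does not say which visit or contrast it covers.
- **That the ANOVA dilutes the treatment effect by averaging in baseline.** This needs baseline as a time level, a constant effect from week 13 and the group main effect as the test. The article states none of these.

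**Conclusion.** The point holds for the continuous secondary outcomes and should be fixed. Section 2.9 contradicts itself: its all-randomised, mixed-model commitment does not fit repeated-measures ANOVA with sphericity steps. Its fallback for non-normal data cannot test BFYS against placebo. This is wrong in the stated text and not detail left to an analysis plan that is not shown.

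The size is about 127 of 848 patients left out of the ANOVA (about 42 to 85 at an assumed 5% to 10% incomplete). This rests on the ANOVA being run in its usual complete-case form and on each dropout missing a visit. The Friedman point rests on how the test is built and needs no assumption; the simulation only illustrates it.

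The primary outcome has its own count regression and is untouched. The secondary outcomes are tested only after it, so the conflict does not threaten the trial's main conclusion.

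**What to change.** Before unblinding, amend section 2.9 for the continuous secondary outcomes:

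- Remove repeated-measures ANOVA, the Mauchly and Greenhouse–Geisser steps, the Friedman test, LSD-t and Tamhane's T2.
- Assign every continuous secondary outcome to the mixed model already named, with arm, visit, arm-by-visit and baseline value. Keep multiple imputation as the sensitivity analysis.
- For clearly skewed scales, specify a transformation or a between-arm rank-based method.
- State one between-arm contrast per outcome to which the promised Bonferroni correction applies, for example week 52, the end of treatment.

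The model is already in the plan and uses the scheduled visits, so no new data are needed. The cost is a dated amendment. Choosing the contrast is a real decision, because the article names no key time point for these outcomes. Recruitment is well advanced (582 enrolled by 17 August 2025) and section 2.8.2 plans an interim efficacy analysis, so people who have not seen unblinded results should make the change. Analysis is scheduled to begin on 1 March 2027. Further modelling choices, such as the covariance structure or a centre term, can be left to the analysis plan.

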### Objective

2.1

The primary objective of this study is to evaluate the efficacy of BFYS granules in reducing the frequency of AECOPD among stable COPD patients with the frequent exacerbator phenotype. Secondary objectives include evaluating the impact of BFYS granules on key clinical outcomes such as the frequency of AECOPD requiring hospitalization, mortality rates, lung function tests, exercise capacity, clinical symptoms and signs scores, quality of life, and health economic analysis. It is expected that BFYS granules will not only reduce the frequency of AECOPD but also improve lung function, exercise capacity, clinical symptoms, quality of life, and demonstrate favorable cost-effectiveness compared to placebo.

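### Section 2.9 sends non-normal continuous secondary outcomes to the Friedman test, which has no treatment-arm term, and names no between-arm test suited to such data

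*Protocol article*

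**What the plan says.** Section 2.9 (Statistical analysis) sets the rule for continuous secondary outcomes: "continuous data will use repeated-measures analysis of variance (for normal distribution) or Friedman test (for non-normal distribution". By section 2.7.2 these outcomes are lung function, symptom and sign scores, six-minute walk distance, CAT and SF-36. For lung function, "Measurements will be conducted at baseline and every 13 weeks during the study period"; the schedule in Table 2 gives five visits (baseline and weeks 13, 26, 39 and 52) for all of them. Of the symptom and sign scores, section 2.7.2 says "Each item will be scored on a 0–3 scale".

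Three further statements in section 2.9 bear on the point:

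- After the Friedman clause comes the sphericity step, "Mauchly’s test will first be applied to assess sphericity for repeated measures", with a Greenhouse–Geisser correction if sphericity fails. Then: "Pairwise comparisons within groups will use the Bonferroni method, between groups the LSD-*t* test (equal variances) or Tamhane’s T2 method (unequal variances".
- On incomplete data: "Missing data will be handled using mixed-effects models for repeated measures as the primary method". The same type of model is named for unequal follow-up, with time as a covariate. No treatment or treatment-by-visit term is stated.
- For every test, p-values and "95% confidence intervals will be reported".

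Section 2.1 (Objective) frames the secondary aims as effects of BFYS. Its list of expected benefits ends with "demonstrate favorable cost-effectiveness compared to placebo".

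**The concern.** The secondary aims are comparisons between randomised arms. The Friedman test is a one-sample, within-patient test of whether visits differ. Run on all patients pooled, it ignores the arms. Run once per arm, it gives two p-values for change over time and no comparison of those changes.

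Both arms receive health education and conventional drugs, so some shared movement from baseline is plausible without any drug effect. A rule that turns shared movement into a significant result would support a treatment claim that randomisation does not support. Secondary outcomes are tested only after a significant primary result, which is when such claims would be made. Bonferroni correction of a p-value for time does not control the error rate of a claim about treatment.

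**Working it through.** There is no stated figure to reproduce. The question is what the assigned test can see.

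**1. The statistic.** With n patients, k = 5 visits and R_j the sum over patients of the within-patient rank at visit j,

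Q = 12 / [n k (k+1)] × Σ_j R_j² − 3 n (k+1).

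No term carries an arm label, so reassigning patients to arms leaves every R_j, and hence Q, unchanged. A numerical check with 848 simulated patients gave Q = 2.389, p = 0.665 both before and after reshuffling the patients. There is also no arm difference in Q around which to build a confidence interval.

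**2. Simulated behaviour.** From the protocol: 359 evaluable per arm (section 2.4), five visits, 1:1 allocation, level 0.05. Assumed: two-sided testing, a log-normal outcome, between-patient log-SD 0.5, within-patient log-SD 0.4, change linear to week 52, 2,000 trials per scenario. These SDs imply a correlation between visits of 0.25 / (0.25 + 0.16) = 0.61 and a total log-SD of √0.41 = 0.64. A 10% fall is then |ln 0.9| / 0.64 = 0.105 / 0.64 ≈ 0.16 SD, and a 5% fall is 0.051 / 0.64 ≈ 0.08 SD. The comparator is a rank-sum (Mann–Whitney) test of change from baseline to week 52 between arms.

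| Scenario (359 per arm) | Friedman, pooled | Friedman, placebo arm | Friedman, BFYS arm | Rank-sum of change, between arms |
|---|---|---|---|---|
| No change in either arm | 5.3% | 5.3% | 5.6% | 4.9% |
| Both arms fall 5% | 43.9% | 23.8% | 23.0% | 5.1% |
| Both arms fall 10% | 98.8% | 81.5% | 81.5% | 5.2% |
| Arms move about 10% in opposite directions | 4.0% | 81.3% | 82.5% | 99.6% |

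At 424 per arm, the shared 10% fall gives 99.6% (pooled) against 5.5% (between arms).

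A separate simulation (360 per arm, correlation 0.6, skewed outcome, shared change of 0.15 SD, 1,000 trials) agrees: 99% pooled, about 85% within each arm, and 4% for a baseline-adjusted arm comparison.

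**3. Reading the test arm by arm.** The arms are independent. Under a shared 10% fall, the chance of significance in the BFYS arm but not in the placebo arm is 0.815 × (1 − 0.8145) ≈ 15%. Under a shared 5% fall it is 0.2295 × (1 − 0.238) ≈ 17%. There is no drug effect in either case.

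**4. Size of the change and the multiplicity rule.** The article does not count the secondary tests. Taking ten as an illustration, the Bonferroni level is 0.05 / 10 = 0.005. A rough check (log-normal, 360 per arm, correlation 0.6, pooled Friedman) gives:

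| Shared change | Rejections at 0.05 | Rejections at 0.005 |
|---|---|---|
| 0.05 SD | 28% | 6% |
| 0.10 SD | 85% | 59% |
| 0.15 SD | about 100% | 97% |

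The percentages move with the assumptions. The absence of an arm term does not.

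**5. Other between-arm methods in section 2.9.** LSD-t and Tamhane's T2 compare means and follow directly on the Mauchly and Greenhouse–Geisser steps, which belong to the analysis of variance. The mixed models are tied to missing data and unequal follow-up, with time as the only covariate mentioned. The article names no rank-based comparison of the arms.

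**The case against.** The strongest reply is that section 2.9 does contain between-group methods. The LSD-t/Tamhane sentence is not expressly limited to normal data, and with 359 to 424 per arm a comparison of means is workable for moderately skewed scores. Mixed models are called the primary method for missing data, within an intention-to-treat analysis by assigned arm. A reader might infer that non-normal outcomes get no between-arm test whatever; the text does not support that. What stands is narrower. The mean comparisons are placed as follow-ups to the branch that the plan's own normality rule sets aside for these outcomes. The mixed-model sentences state no treatment term, and if they are the main analysis they conflict with the ANOVA/Friedman sentence.

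A reader might also infer that most outcomes will end in the Friedman branch. The article names no normality test or threshold and does not say whether the symptom items are summed, so the frequency is unknown. Bounded 0–3 items make it likely for symptom scores; for CAT, SF-36, lung function and walk distance it is not shown.

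The rate near 99% should not be read as the trial's false-positive rate. It belongs to one assumed shared change at an unadjusted level, whereas the plan gates secondary outcomes behind the primary and then applies Bonferroni. The opposite-direction scenario is a special case too: the effects cancel only when the movements nearly balance and the arms are pooled.

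Finally, the promise of intervals covers all tests and does not specify the arm difference, so it is not breached outright. The Friedman test still cannot supply the interval a reader needs.

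**Conclusion.** The point holds in this form. For continuous secondary outcomes judged non-normal, the assigned test cannot answer the comparison with placebo and can turn a change common to both arms into a significant result. The plan names no between-arm test suited to those data and leaves three overlapping methods unreconciled. That conclusion rests on the structure of the test. The size is illustrative: depending on the assumed shared change (0.05 to 0.15 SD), the pooled test rejects in 28% to about 100% of trials at 0.05 and in 6% to 97% at 0.005, with no drug effect, while a between-arm test stays at 4% to 5% at the 0.05 level.

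The reach is limited. The primary outcome and hospitalised exacerbations go to Poisson or negative binomial regression and mortality to logistic regression, so this clause touches none of them. This should be fixed, but it does not threaten the trial's main conclusion.

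**What to change.** In section 2.9 and the analysis plan, replace the Friedman branch with the mixed model for repeated measures already named there. State fixed effects for arm, visit and arm-by-visit, and report the week-52 arm difference with its 95% confidence interval. Say how this model relates to the repeated-measures ANOVA and the LSD-t/Tamhane comparisons, so that each outcome has one main between-arm analysis. If a rank-based check is wanted, compare change from baseline between arms with a Wilcoxon rank-sum test as a sensitivity analysis.

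The cost is wording before database lock. No new data, visits or patients are needed, and the article schedules analysis to begin on 1 March 2027.
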